#### **4.9a Data analysis**

We will use intent-to-treat analyses to compare outcomes between the intervention and control groups at endline. Our analyses will include subgroup analyses by baseline risk behavior level. We will perform linear or logistic regressions to estimate the effect of the intervention on each outcome of interest, and will include control variables for selected baseline characteristics and for all variables used in randomization.

#### **4.9b Sample size and power calculations**

Because this is a pilot study, we may not have sufficient power to detect statistically significant effects on all of the primary outcomes. We aim to recruit a sample size sufficient to detect a 15 percentage point increase in probability of increasing the savings balance (outcome 1), with 80% power and  $\alpha=0.05$ . The necessary sample size will be 200 participants if we assume that 10% of participants in the control groups will have an increase in savings between baseline and endline. With a sample size of 300 participants and 50% of participants in the control group having an increase in savings, we will by 80% power to detect a difference of  $\geq 16$  percentage points in the probability that savings increases due to the intervention. This pilot project is intended to assess the feasibility and acceptability the prize-linked savings intervention and will also generate vital preliminary data on likely effect sizes on important economic and health outcomes. It will also aid in the development of recruitment procedures and data collection tools that will be used for a larger scale-up of the intervention if the pilot results are promising. As such, we will balance the need for a large enough sample to detect statistically significant changes in our primary outcome with the need to keep the pilot study at a small scale.

### **5.0 ETHICAL CONSIDERATIONS**

#### **5.1 Potential risks to human subjects**

The risks to study participants are minimal as the project primarily involves baseline and follow-up survey questions and an intervention to promote financial savings. For some participants there is a possibility of experiencing distress from being asked to answer personal survey questions about sexual behavior.

#### **5.2 Adequacy of protection against risks**

##### **5.2.1 Informed consent**

Informed consent will be obtained from all participants by trained research assistants. Because some participants may not be able to read at a level enabling them to understand the consent form, the survey team will offer to read the letter in its entirety and will discuss the consent process in detail verbally. The research assistants will find a private place; carefully explain the nature and purpose of the study to each potential participant, potential risks and benefits, compensation for participation, and will describe the two study groups to which participants will be randomized. The consent process will be offered in English, Kiswahili, or Dholuo (as per the

participant's preferences). The banking partner will also obtain consent from respondents to share their savings data with study staff. Our study team has prior experience in obtaining informed consent for research and clinical trials within the cultural context of in Kenya. For those who cannot sign the informed consent form, they will be asked to make a mark with the pen or to use an inkpad and make a thumbprint indicating their choice to participate, and a witness will also sign indicating that free and informed consent was given. The informed consent procedure has been designed to maximize understanding of potential risks. Participants will be told that they may decline to participate at any point. The consent procedure will be carried out at baseline, prior to administering the baseline survey. For those who consent, the survey will take place immediately after the consent procedure. For those who are unsure, the survey team will attempt to answer their questions and will work with the potential respondent to find another time on a subsequent day for a follow-up visit.

In order to protect against risks associated with answering sensitive questions, all participants will be reminded that they are not obligated to answer any survey questions that they do not feel comfortable answering.

### **5.2.2 Maintaining privacy and avoiding stigmatization**

Participants will be interviewed during the day, primarily near the locations where they work. Interviewers will make every effort to find a secluded location where others cannot overhear the interview. Prior to any questionnaire modules that ask about sexual behavior or other potentially sensitive information, participants will be reminded that they may skip certain questions if they do not wish to answer.

### **5.2.3 Data security**

We will develop standard operating procedures for data security and confidentiality procedures at collection, transfer, entry and storage levels, and make these readily accessible to all staff members who have access to confidential study data.

Individual study identifiers will be assigned to participants at enrollment. Data will not be able to be used to identify individuals directly. To protect personal information (name, phone number), data collected in surveys will be encrypted and de-identified.

All study tablets used for data collection will be encrypted and password protected. They will be autonomously monitored so that the tablet can be wiped clean in the case of a tablet going missing. All electronic study data will be stored on a secure server with access limited only to authorized staff. All computers and servers will be encrypted and password-protected with limited access.

Physical data collection forms will be stored at IPA offices and will be kept under lock and key by the Study Coordinator. They will be accessible only to the PIs and Coordinator. A key linking identification numbers of respondents to the respondent identity will be kept in file separate from the main dataset, will only be accessed by key study personnel, and will be encrypted. This key will be destroyed once data collection is complete. At the end of the study, any data containing identifying information will be kept for up to 5 years for electronic version and up to 2 years for paper forms, including consent forms.

### **5.2.4 Institutional Review Board approval**

Approval from the University of Pennsylvania institutional review board and the Maseno University institutional review boards (IRBs) will be obtained prior to initiation of any study activities. All study staff are required to undergo training in human subjects research, and good clinical practice.

### **5.3 Potential benefits of the proposed research to the participants and others**

Participants may directly benefit from the study: a small number of participants will have the opportunity to win prizes if they choose to save money over the course of the study. Prizes will be allocated at random among the set of participants who increase their savings during the study. Participants may also experience benefits from increased savings even if they do not win prizes.

Participants will contribute to a body of knowledge about effective interventions to increase savings and to reduce HIV risk-related behaviors among men. This can indirectly benefit those who may be targeted by future interventions based on this body of evidence, including adolescent girls and young women who face high HIV risk stemming from age-disparate relationships and transactional sex.

### **5.4 Importance of the knowledge to be gained**

Findings from the pilot trial may reveal new ways to influence the HIV epidemic in priority regions where it continues unabated and will directly inform the design of a larger-scale study that focused on ways to achieve changes in health and economic behaviors. Several aspects of this study would fall directly within the HIV prevention priorities laid out by NIH and countries in eastern and southern Africa. The project has potential to identify sustainable and scalable ways to promote better economic and health outcomes.

## **6.0 LIMITATIONS**

We recognize potential critiques of the proposed project and will attempt to address these to the best of our ability. A primary limitation in our study is that it is a small pilot project, therefore we may not be able to answer all questions with a high level of statistical significance and we may not be able to perform many sub-group analyses due to sample size limitations. This will be resolved if we proceed to a future scaled-up study. In addition, some of our outcomes (such as sexual behavior) will be self-reported. This is not a major problem, however, because we will obtain these measures in both study groups so we can compare changes among and between the groups.

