## **4.5 Intervention group**

Research assistant will explain the structure of the lottery prizes to participants randomized to the lottery incentive group. Participants will be told their chance of winning monetary rewards will be based on the amount by which their account balance goes up (e.g. for every 100 Ksh by which savings increases, participants get an entry into a lottery for monetary rewards.) This type of prize-linked savings intervention has been shown to promote savings in other settings. During the intervention period, participants' savings account activity will be checked at regular intervals and lottery prizes will be determined at these intervals. Participants will learn about the lottery outcome via SMS and prizes will be deposited directly into their savings accounts.

Other intervention components may include education materials to explain how the prize-linked savings incentives work and that emphasize the potential benefits of saving money (having greater ability to cope with setbacks, build or upgrade their homes, pay school fees, buy farm

inputs, buy more motorbikes for use in business, or start a different business; etc.). Participants in the intervention group will be encouraged to have more consideration for their future health and economic status, as this may motivate them to save more money. They will also be encouraged to consider the opportunity and health cost of their expenditures on alcohol and transactional sex and not miss the opportunity to win prizes by saving money.

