#### **4.6 Comparison group**

During the study period, participants' savings account activity will also be tracked at regular intervals, but they will not be eligible to receive lottery-style prizes. They may instead receive interest on the amount they have saved at a standard rate that is determined by the banking partner.

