#### **4.7 Data collection activities**

Structured questionnaires will be administered to all participants at the time of enrollment (baseline) and at study completion. Data will be collected by a team from Innovations for Poverty Action (IPA), which has led a number of household surveys in the Nyanza region. Trained research assistants from IPA will administer these questionnaires using tablet computers. Participants will receive a small amount of compensation for the time required to complete each survey.

*Baseline data collection:* A baseline questionnaire will collect information on demographic characteristics, employment and income, assets and savings, consumption and expenditures, self-reported sexual behavior, alcohol and substance use, HIV risk perceptions, and questions about financial stress, future orientation, and expectations. Sexual behavior questions will inquire about past engagement in transactional sex (defined broadly to include financial and non-financial transfers from the partner to the woman, approximate age of sexual partners).

*Interim data collection:* Additional contact from the survey team may occur at regular intervals during the intervention period. These intermittent contacts may occur via SMS or in person and are expected to take only a few minutes.

*Endline data collection:* An endline survey with similar content as the baseline will be administered about 3-4 months after study enrollment in order to measure economic and health outcomes that have the potential to be affected by the intervention..

The questionnaire modules will be based on questionnaires that have been used in other studies in the Nyanza region and on surveys such as the Demographic and Health Survey and the World Bank's Living Standards Measurement Surveys.

*Qualitative interviews:* In addition to the baseline and endline surveys, we may conduct in-depth interviews with up to 20 men to explore perceptions of the prize-linked savings intervention. Beyond exploring the extent to which the intervention motivated men to save money and change their health and economic behavior, the interviews will also assess other factors that influence men's decisions – including barriers to saving such as beliefs about mortality risks in the future.

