#### **4.8 Outcomes**

We will be interested in assessing four primary outcomes:

1. Increase in savings balance: This is a binary variable equal to 1 if the respondent's savings balance increased over the study period, and zero otherwise.
2. Change in savings balance over full study period: Similar to outcome 1, but a continuous measure of the net increase or decrease in savings balance over the study period.
3. Expenditures on alcohol

4. Participation in transactional sex
5. Expenditures on transactional sex

We will additionally assess the following secondary outcomes:

1. Savings: Net increase in both the savings balance and in self-reported total savings from all sources, in each lottery period and over the entire study period.
2. Expenditures on food items
3. Expenditures on non-food items

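### Measuring self-reported outcomes in both arms does not make reporting bias a minor problem, because under-reporting may differ by arm and would probably favour the intervention

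*Protocol*

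**What the plan says.** Section 6.0 (Limitations) concedes that "some of our outcomes (such as sexual behavior) will be self-reported". It then sets the matter aside: "This is not a major problem, however, because we will obtain these measures in both study groups", on the ground that changes can be compared among and between the groups.

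Section 4.5 gives the intervention group more than a lottery. "Participants in the intervention group will be encouraged to have more consideration for their future health and economic status", and, on the behaviours that the survey later asks about, "They will also be encouraged to consider the opportunity and health cost of their expenditures on alcohol and transactional sex". Section 4.6 describes no such messaging for the comparison group. Their accounts are tracked and they may earn standard interest, "but they will not be eligible to receive lottery-style prizes".

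The numbered list of primary outcomes in section 4.8 includes "Expenditures on alcohol" (outcome 3), "Participation in transactional sex" (outcome 4) and spending on transactional sex (outcome 5). The only source described for these is the questionnaire. Section 4.7 says how it is given: "Trained research assistants from IPA will administer these questionnaires using tablet computers".

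**The concern.** An arm comparison is protected from misreporting only if the misreporting is the same in both arms. Here one arm receives a message about the cost of two behaviours and is then asked by study staff whether it engaged in them. A man who has heard that message has a reason to under-report that a control man does not have.

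At stake is the reading of three primary outcomes, the ones that carry the trial's HIV rationale. A fall in reported alcohol spending or transactional sex could be partly or wholly a change in what men are willing to say. Section 4.9b says the pilot will supply data on likely effect sizes, and section 2.0 says these feed the design of a larger trial. A reporting artefact would pass into that design, and a larger sample would not remove it, because it is bias and not noise.

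**Working it through.** **1. Does the design give a reason for unequal error?**

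| Feature | Intervention | Comparison | Protocol section |
|---|---|---|---|
| Message on the cost of alcohol and transactional sex | Yes | None described | 4.5, 4.6 |
| Encouragement to think of future health | Yes | None described | 4.5, 4.6 |
| Knows own arm | Yes: lottery explained, results sent by SMS | Yes: both groups described at consent, no lottery | 4.5, 4.6, 5.2.1 |
| Endline questions put by research assistants | Yes | Yes | 4.7 |
| Private setting, right to skip questions | Yes | Yes | 5.2.1, 5.2.2 |

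The first two rows differ by arm. The last row is common to both, so it does not address a difference in error. No blinding of endline interviewers is described. The timeline in section 8.0 has intervention delivery and the follow-up survey both in November, so the message can be recent when men are asked.

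**2. The plan's own figures.** Section 4.9b concerns outcome 1 only. With two-sided α = 0.05, 80% power and no continuity correction, 10% against 25% needs 100 per arm, 200 in total, as stated. With 150 per arm, 50% against 66% has power 0.805, also as stated. Both reproduce, and neither bears on outcomes 3 to 5. They fix only the method and the 150 per arm used below.

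**3. Size, by illustration for outcome 4.** From the protocol: about 300 men, equal allocation, α = 0.05 (two-sided assumed). Assumed, because the protocol gives no figure: true participation p, denial c common to both arms, excess denial u in the intervention arm, and no true effect.

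Reported proportions: control P₀ = p(1 − c); intervention P₁ = p(1 − c)(1 − u). False reduction: d = P₀ − P₁.

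Rejection probability = Φ((d − 1.96·s₀)/s₁) + Φ((−d − 1.96·s₀)/s₁), with s₀ = √(2P̄(1 − P̄)/n), s₁ = √((P₀(1 − P₀) + P₁(1 − P₁))/n), P̄ the mean of P₀ and P₁, and n = 150.

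Example, p = 0.40, c = 0, u = 0.20: P₀ = 0.40, P₁ = 0.32, d = 0.08, s₀ = 0.0554, s₁ = 0.0552. The first term is Φ((0.08 − 0.1086)/0.0552) = Φ(−0.52), about 0.30; the second is negligible.

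| p | Common denial c | Excess denial u | P₀ vs P₁ | False reduction (points) | Rejects at 5% |
|---|---|---|---|---|---|
| 40% | 0 | 5% | 40.0% vs 38.0% | 2.0 | 6.5% |
| 40% | 0 | 10% | 40.0% vs 36.0% | 4.0 | 11% |
| 40% | 0 | 20% | 40.0% vs 32.0% | 8.0 | 30% |
| 40% | 0 | 30% | 40.0% vs 28.0% | 12.0 | 59% |
| 40% | 20% | 10% | 32.0% vs 28.8% | 3.2 | 9% |
| 40% | 20% | 20% | 32.0% vs 25.6% | 6.4 | 23% |
| 40% | 20% | 30% | 32.0% vs 22.4% | 9.6 | 46% |

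With c = 0, p from 20% to 60% and u from 5% to 30%, the false reduction runs from 1 to 18 points and the rejection rate from 5.5% to 88%.

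**4. Does equal error behave as section 6.0 assumes?** Under the null, yes: with u = 0 the difference stays at zero. A true 40% against 30% shrinks from 10 points to 9, 8 or 7 with 10%, 20% or 30% denial in both arms. Equal error therefore dilutes a real effect but creates no false one.

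**5. Does comparing changes help?** The message comes after baseline, so excess denial enters only at endline. Let both arms report p(1 − c) at baseline. The difference in change is [p(1 − c)(1 − u) − p(1 − c)] − [p(1 − c) − p(1 − c)] = −p(1 − c)u. For p = 0.40 and c from 0 to 20%, this is −4.0 to −3.2 points at u = 10% and −8.0 to −6.4 at u = 20%. The baseline terms cancel and the bias remains.

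**The case against.** The protocol has no data on reporting error, so a reader might infer that the bias is established to differ by arm and to favour the intervention. The documents do not support that. The arm-specific message gives good reason to expect that direction for alcohol and transactional sex, but neither the difference nor its size is shown. Some pressure is also shared, since all men hear the purpose of the study at consent and answer the same modules.

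Nor does the text say that men are coached against these behaviours. They are encouraged to consider the costs, in a sentence that ends with the chance of winning prizes. It is also tempting to read the staff who explain the lottery and the endline interviewers as the same people. They share a job title, but overlap is not documented and the protocol names nobody as the deliverer of the encouragement. What stands is that nothing keeps the roles apart.

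The illustration can be criticised too. Truthful reporting by all controls is the less favourable case, and common denial lowers every figure. At 5% excess denial the test is close to its nominal level. The figure of 150 per arm comes before any dropout, and spending outcomes 3 and 5 are not modelled. All of this is fair, so the numbers show what could happen, not what will.

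Finally, this is a pilot, sized on outcome 1, that warns of limited power for other primary outcomes. That limits what it claims on outcomes 3 to 5. It does not make the sentence in section 6.0 correct, and low power is no defence against bias.

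**Conclusion.** The reasoning in section 6.0 is wrong and should be corrected. Measurement in both arms removes only equal error, and the protocol's own section 4.5 gives a reason to expect unequal error in an open trial with interviewer-administered questions. Comparing changes does not help.

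Exposed are primary outcomes 3, 4 and 5, and among the secondary outcomes self-reported total savings and food and non-food spending. Outcomes 1 and 2 are not exposed in so far as they rest on the savings data that the banking partner shares (section 5.2.1).

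The size cannot be settled from the document. At 40% true participation and 10% to 30% excess denial, the false reduction is 4 to 12 points with truthful controls and 3.2 to 9.6 points with 20% common denial. The corresponding rejection rates are 11% to 59% and 9% to 46%. These rest on assumed prevalence and denial, no true effect, 150 men analysed per arm and a two-sided 5% test.

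A reader might also infer that outcomes 3 to 5 cannot remain primary. That does not follow: these behaviours are the trial's stated purpose, and a new label would not reduce the bias.

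**What to change.** 1. **Section 6.0:** replace the sentence with a statement that self-report bias may differ by arm, probably favouring the intervention, and that comparing arms or changes does not remove it.
2. **Section 4.7:** within the existing team, do not let an assistant who explained the intervention to a man conduct his endline interview. Ask the alcohol and sexual-behaviour modules before any savings or lottery questions. This reduces the bias but does not remove it, because the man still knows his arm. It has to be settled before endline, since no later analysis can restore it.
3. **Section 4.9a:** for outcomes 3 to 5, report a tipping-point analysis giving the excess under-reporting in the intervention arm that would remove each observed effect, and interpret those outcomes in that light.

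Relabelling outcomes 3 to 5 as secondary is optional and not part of this fix. The cost is a wording change, minor rostering and question-order work, one sensitivity analysis, and more cautious conclusions on outcomes 3 to 5. The protocol does not state the size of the field team, so the rostering needs a check at each site.

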## **7.0 DISSEMINATION OF RESEARCH FINDINGS**

The results will be shared with the study site staff and other stakeholders in relevant forums. The results will also be presented at local and international meetings and conferences where other researchers and policymakers are present, particularly those working on HIV prevention and treatment. In addition, we will prepare manuscripts and submit them to peer-reviewed journals for publication and wider dissemination. No individual identities will be used in any reports or publications resulting from the study.

